#### Economic evaluation

For the economic evaluation, missing cost and effect data will be imputed using multiple imputation according to the algorithm developed by van Buuren et al. [63]. Linear regression analyses will be used to estimate cost and effect differences between the intervention group and the control group while adjusting for confounders if necessary. Bias-corrected accelerated bootstrapping with 5000 replications will be used to estimate statistical uncertainty surrounding the cost and effect differences. Incremental cost-effectiveness ratios (ICERs) will be calculated by dividing the difference in costs between the groups by the difference in effects. Bootstrapped cost-effect pairs will be plotted on cost-effectiveness planes to show the uncertainty surrounding the ICER. Cost-effectiveness acceptability curves will be estimated to show the probability that the In Balance intervention is cost-effective compared to control for different willingness-to-pay values (i.e. the amount of money that society is willing to pay per additional unit of effect).

### Adverse events

Adverse events are defined as any undesirable experience occurring to a participant during the study, whether or not considered related to the In Balance intervention or the trial procedure. All adverse events reported spontaneously by the participant or observed by the investigator or staff will be recorded. Occurrence of adverse events will be assessed during the monthly telephone calls and for the intervention group during the In Balance intervention by the therapist.

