### Recruitment, randomization, blinding and treatment allocation

Recruitment will be done via flyers, advertisements in local papers, folders distributed through supermarkets, pharmacists, community centres, general practitioners, at annual flu shots, and via personal invitations by In Balance therapists and general practitioners. Participants will be randomized into the intervention group or the control group using block-randomization to balance the size of the two groups. Randomization will be stratified according to frailty. We aim to include 30–50% of the participants in the pre-frail subgroup and 50–70% in the non-frail subgroup in both the intervention and control group. As soon as one of the subgroups starts to outnumber the other subgroup, we will only target the underrepresented subgroup for recruitment. Two hundred fifty-six sealed envelopes in blocks of 10 (5 envelopes per group) will be prepared by an independent investigator. These sequentially numbered envelopes contain a random computer-generated unique identification number. A second matching envelope contains the group information. All investigators and assessors involved in this study will be blinded to group assignment until completion of statistical analyses. Due to the nature of this study, participants and therapists cannot be blinded to group allocation. Participants will be informed orally about their allocation and therapists will receive the names of those participants who will participate in the In Balance intervention.

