### Intervention

The In Balance intervention is a fourteen-week group programme for older adults at risk of falls and will be provided by registered and certified physical therapists and exercise therapists [36]. The aim of the intervention is to reduce falls by increasing awareness, balance and strength by combining educational and exercise components. The intervention consists of three phases. The first phase (week 1) comprises one information meeting about physical activity, the impact a fall can have on a person’s life and health, and the purpose of the In Balance intervention. In the second phase (week 2–4), there are three weekly educational meetings about increasing awareness of one’s fall risk and balance disturbance, increasing knowledge about how to implement effective fall prevention methods and getting acquainted with the upcoming training weeks. The third phase (week 5–14) consists of a physical exercise programme with two one-hour training sessions per week. Exercises are derived from principles of Tai Chi, with balance and strength elements and with emphasis on standing strong and shifting weight. Education and Tai Chi exercises are known to be effective in reducing the incidence of falls [37–39]. After each session, the participants receive homework, consisting of conducting exercises learned during the training sessions and reading parts of the textbook belonging to the In Balance intervention. Participants are expected to spend about one hour per week on this homework, distributed over several days. The 3 phases of the intervention are summarized in Fig. 1.

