### Control group

The control group will receive written general physical activity recommendations in the form of a flyer. This flyer contains advice on physical activity levels, strength and balance for older adults. For example, a minimal amount of 150 min of moderate to vigorous physical activity per week is recommended, distributed over several days. Also muscle and bone strengthening activities such as walking stairs and balance exercises at least twice per week are advised. Moreover, the health benefits associated with physical activity are explained. These recommendations follow the Dutch Guidelines for Physical Activity [40]. To minimize study attrition, participants of both the intervention and control group will receive regular newsletters during the study and a personal advise on (changes in) physical performance after ending of the study.

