### Data collection and outcome measures

#### Primary outcome measure

The primary outcome in this study is the number of falls, with or without injuries, assessed with fall diaries and monthly follow-up telephone calls, including questions on the causes, circumstances and consequences of falls. This combination of pro- and retrospective data collection follows guidelines for conducting fall prevention trials [41].

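### Therapists record adverse events in the intervention group only, so a by-arm table that pools all sources would be inflated in that arm

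*Protocol article*

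**What the plan says.** The Adverse events section of the protocol article defines an event very broadly: "Adverse events are defined as any undesirable experience occurring to a participant during the study", whether or not it is thought to be related to the programme or the trial procedures. It describes two kinds of collection.

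- **Passive:** "All adverse events reported spontaneously by the participant or observed by the investigator or staff will be recorded". No arm is named.
- **Active:** "Occurrence of adverse events will be assessed during the monthly telephone calls and for the intervention group during the In Balance intervention by the therapist". The monthly calls apply to both groups and the therapist to one.

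Three other sections bear on this. Under Recruitment, randomization, blinding and treatment allocation: "Due to the nature of this study, participants and therapists cannot be blinded to group allocation". Under Control group: "The control group will receive written general physical activity recommendations in the form of a flyer", so controls have no therapist. The Primary outcome measure section fixes how falls are counted: "The primary outcome in this study is the number of falls, with or without injuries, assessed with fall diaries and monthly follow-up telephone calls", with no source that depends on the arm.

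The article does not say how events recorded only by a therapist will be tabulated. It does not exclude falls from the adverse event definition.

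**The concern.** Who can notice an event depends on the arm. During the programme an intervention participant is regularly seen by someone asked to note adverse events, and a control participant is not. Under so broad a definition, minor complaints count. These are the events that a monthly call is most likely to miss and that a person present twice a week is most likely to note. The extra observers also know the allocation.

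A by-arm table that adds all sources together would then lean against the intervention even if the true event rates were equal. Even without a planned test, readers will compare the two columns of such a table. If the source of each event is not captured when it is recorded, no later analysis can remove the therapist-only events.

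**Working it through.** The plan gives no figure for this point, so there is none to reproduce. The check is a contact count and an illustration on assumed capture rates.

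**Contacts during the programme** (Intervention section). There is one information meeting in week 1 and three educational meetings in weeks 2–4. For the rest, "The third phase (week 5–14) consists of a physical exercise programme with two one-hour training sessions per week".

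- Therapist contacts: 1 + 3 + 10 × 2 = 24.
- Monthly calls in the same period, either arm: 14/52 × 12 = 3.2, so about three.

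The two counts are not like for like. A call asks about a whole month, whereas a session lasts about an hour. They show that the extra channel is regular, but they do not measure how much it adds.

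**Model.** Assume equal true event rates in both arms, constant over 12 months.

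- s = share of events caught by the channels common to both arms (assumed).
- t = share of the events missed by those channels that the therapist catches during the programme (assumed).
- f = share of follow-up covered by the programme = 14/52 = 0.269.

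Apparent ratio, intervention to control, when all sources are pooled:

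- During the programme: [s + (1 − s)t] / s
- Over 12 months: [f(s + (1 − s)t) + (1 − f)s] / s, which simplifies to 1 + f × (programme ratio − 1)

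**Two worked cases, both with t = 0.5.**

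- s = 0.70: capture rises to 0.70 + 0.30 × 0.5 = 0.85. Programme ratio 0.85/0.70 = 1.21. Over 12 months 1 + 0.269 × 0.214 = 1.06.
- s = 0.50: capture rises to 0.50 + 0.50 × 0.5 = 0.75. Programme ratio 0.75/0.50 = 1.5. Over 12 months 1 + 0.269 × 0.5 = 1.13.

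**Range for t from 0.25 to 0.8.**

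| s (assumed) | Ratio in the 14 weeks | Ratio over 12 months |
|---|---|---|
| 0.5 | 1.25 to 1.80 | 1.07 to 1.22 |
| 0.7 | 1.11 to 1.34 | 1.03 to 1.09 |
| 0.8 | 1.06 to 1.20 | 1.02 to 1.05 |
| 0.9 | 1.03 to 1.09 | 1.01 to 1.02 |
| 1.0 | 1.00 | 1.00 |

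The direction is the same throughout: more recorded events in the intervention arm. The effect vanishes if the common channels miss nothing, or if only events from those channels are compared.

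**The case against.** The strongest reply is that the article announces no between-group analysis of adverse events. They are not listed among the primary or secondary outcomes, and the analysis section covers only those outcomes. Tabulation by source is usually settled in the analysis plan or on the case report form, neither of which is shown. Therapist monitoring of an exercise programme is ordinary safety oversight. The Data management section mentions documentation of each training session and a logbook per participant, so session-level entries may already be distinguishable.

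Much of this stands. No announced analysis is wrong, and therapist reporting should continue. But the rule that differs by arm is stated in the protocol; it is not a detail left open. The remedy also has to be in place at collection, and the article does not say that the source of each event is kept.

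A reader might infer three stronger things that the documents do not support.

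- **That any between-arm comparison of adverse events is biased.** A comparison based on the monthly calls uses the same active channel in both arms, and the therapist channel does not touch it.
- **That in-session falls are a recording artefact.** Only the intervention group attends sessions, so a fall there is a real consequence of exposure. The Discussion itself notes that activity can raise exposure to fall risk.
- **That the primary outcome is pulled toward no effect.** Falls are "assessed with fall diaries and monthly follow-up telephone calls, including questions on the causes, circumstances and consequences of falls". Therapist reports could matter only if they were added to that count, and nothing in the article provides for this.

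It is also fair to object that ratios for the 14 weeks alone show the problem in its least favourable window. The 12-month figures are much smaller.

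**Conclusion.** The concern holds for a by-arm tabulation that pools all sources, and only for that. Such a table is open to differential ascertainment that inflates the intervention arm. The size is unknown because the documents give no capture rates. On assumed capture of 70% against 85%, or 50% against 75%, the apparent ratio is 1.21 to 1.5 during the programme and about 1.06 to 1.13 over 12 months. These figures rest on equal and constant true event rates, and on the therapist channel acting only during the 14 weeks. They also take the passive reporting route to work alike in both arms.

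The primary falls count is not shown to be biased. This is a modest point, worth acting on because the correction is nearly free and cannot be made afterwards if the source was never recorded.

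**What to change.** 1. Add a source field to the adverse event form: monthly call, spontaneous report, observation at an assessment visit, or therapist.
2. State that any between-group comparison of adverse events uses only the channels common to both groups, that is, the monthly calls and other reports that do not depend on the arm.
3. Report therapist-recorded events separately and descriptively for the intervention group, with in-session falls shown there as exposure-related harms.
4. Confirm in one sentence that the primary falls count uses diaries and monthly calls only, and that an in-session fall reported through either of these still counts.
5. Keep therapist safety reporting as it is.

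The cost is one field on the form and a few sentences in the plan. A few therapist-only events move out of the comparative table into a separate one. A therapist entry reveals the allocation, so the field should be hidden from blinded investigators and assessors until the analyses are complete.

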### Trial status

Enrolment into the study will start on September 1, 2021. We plan to complete the recruitment and data collection at baseline by September 2022, with a 12 months follow-up period on falls incidence and incidence of fall-related injuries until September 2023. This study has been registered with the Netherlands Trial Register on 13 February 2021 (NL9248).

## Discussion

This paper describes the design of a (cost-)effectiveness study comparing an implemented group-intervention to prevent falls, In Balance, with general written physical activity recommendations. Exercise programmes have been proven to be effective in preventing falls. In particular, interventions containing challenging balance and functional elements result in the most beneficial outcomes [64–66]. The In Balance intervention includes both balance and physical exercises, and is already proven to be effective in reducing the number of falls among a frail, residential population [24]. Since the target population and duration of the In Balance intervention programme intervention have been adjusted after broader implementation, re-evaluation of the (cost-)effectiveness of the current In Balance intervention is urgently needed.

One strength of this study is that we re-evaluate the widely implemented In Balance fall prevention intervention. In this evaluation, we will stratify for frailty status, which allows us to investigate the impact of the In Balance intervention for different target groups on which the intervention has been extended since implementation. Another strength is that, besides investigating the effectiveness on falls and fall-related injuries, we also study the cost-effectiveness of the In Balance intervention. Little research has been conducted examining the cost-effectiveness of fall prevention interventions in general and no research has been done before on the cost-effectiveness of the In Balance intervention specifically [26]. The cost-effectiveness analysis will indicate whether the added health benefits of the In Balance intervention outweigh the costs.

An additional strength of this study is that we do not only take falls and fall-related injuries into account, which have a large impact on the individual and healthcare, but we will also investigate multiple secondary outcomes such as physical functioning, physical activity, quality of life and other self-reported outcome measures [18]. Despite the health benefits of physical activity, the paradoxical increase in exposure to fall risk should also be taken into account when evaluating falls prevention interventions [67]. Although this study is not powered for the secondary outcome measures, analysis of these outcomes will nevertheless provide insights that are useful to gain more knowledge about the underlying mechanisms of the In Balance intervention on a potential reduction of falls and fall-related injuries. For example, physical activity improves balance control and muscle and bone strength and thus is expected to decrease the number of falls and fall-related injuries [68–71].

This study also includes a process evaluation, to collect information that will be relevant for further implementation of the intervention. Not part of this protocol, but additionally to the process evaluation, we consider focus groups with participants of the intervention group, therapists and other stakeholders to obtain facilitating and hindering factors for implementation. These factors can be taken into account when implementing the outcomes of the study described in this research protocol.

Several challenges of this study need to be mentioned as well. First, the inclusion of 256 participants in this trial, both non-frail and pre-frail, will be challenging. For recruitment, we will involve therapists and their local network over diverse neighbourhoods. Due to the COVID-19 situation, the inclusion of sufficient participants will be extra challenging. We expect that participants may be reticent when considering participating in the In Balance intervention, although the majority of our target population is expected to be vaccinated at the start of our study. Moreover, the social component of the In Balance intervention can be a facilitating factor to participate in this study. In a recent inventory among several In Balance therapists on conducting the In Balance intervention in times of COVID-19, therapists indicated that the In Balance intervention can be conducted while taking the COVID-19 measures into account.

Drop out during follow-up is considered as a threat in this study, particularly in controls due to a lack of attention. To minimize attrition in both the intervention and control group, participants will be closely involved in the study by receiving regular newsletters and a personal advise on (changes in) physical performance after ending the study. In addition, we expect that older adults will appreciate the personal contact during the measurement moments and monthly telephone calls. This personal contact keeps participants involved in the study and lowers the risk of drop out [72]. Another challenge is that even though In Balance therapists will be trained intensively to tailor the level of physical exercises to each individual participant, there will be variance in the training progression of participants in this trial. By training the In Balance therapists and by developing and using standard operating procedures, this variance will be limited. Moreover, this variance represents clinical practice and allows individualized training.

This study includes a considerable number of outcome measures. To limit the burden for participants as much as possible, they will receive questionnaires in their own environment so that they can fill them in in their own time. The physical outcome measures will be assessed at a location in the municipality of the participant and will take about one hour. With the collection of data on the number of falls, we depend on the memory of the participants, with the risk of recall bias. However, we will use an approach consisting of monthly telephone calls in addition to a fall diary, which is considered the most optimal approach to minimize recall bias when reporting the number of falls and fall-related injuries [41]. By personal calls, we will be able to collect detailed information on the causes, circumstances and consequences of falls.

In summary, this trial will provide insight into the clinical and societal impact of an implemented and adjusted Dutch fall prevention intervention and thus has major benefits for older adults, society and health insurance companies. If the In Balance intervention is effective in reducing the number of falls, there are major potential benefits to older adults and the community. Preventing falls could reduce adverse health outcomes, such as disability, hospitalisation and the associated costs [3, 8–11, 16]. Enhanced mobility is expected to improve functioning and result in higher quality of life [8–11]. If cost-effectiveness can be shown, implementation of this intervention will result in more efficient utilisation of health services. Moreover, health insurance companies can make an informed decision on whether the intervention becomes or stays part of insured healthcare. Thus, results of this study will inform healthcare professionals, investigators, and policy makers about timely and (cost-)effective prevention of falls in older adults.

## Data Availability

Only the investigator and study coordinator will have access to the pseudonymised final full trial dataset. A minimal dataset that allows to interpret, replicate and build upon the findings will be available from the corresponding author on reasonable request.
